## Section 1: Administrative information

### 1. Title and Trial registration

This document is a statistical analysis plan of a national retrospective (cross-sectional study) of patients with locally advanced lung cancer treated with definitive radiotherapy: to identify if calcium scoring is a predictor for overall survival and the role of irradiation of heart and substructures. As the trial is a retrospective study, the study is not registered at [clinicaltrials.gov](https://clinicaltrials.gov).

### 2. SAP version

This SAP was finalized on June 2023 and is based on the same study population as the study "Does Coronary artery calcium score have an impact on overall survival for locally advanced non-small cell lung cancer treated with definitive radiotherapy" [2] The extension in the current study includes irradiation of the whole heart and substructures to predict overall survival. The SAP is performed after data is retrieved from the Danish Lung Cancer Registry. However, no data analysis on irradiation dose to the heart has been performed at the time of SAP completion. This SAP is version 1.0.

### 3. Protocol Version

The study is part 3 of a Ph.D. project based on the Ph.D. project protocol version 3.

### 4. SAP Revision – revision history, with justification and timing

No changes have been made since version 1.0 was finalized.

# Section 2: Introduction

## 7. Background and rationale

Locally advanced non-small cell lung cancer (LA-NSCLC) is treated with definitive radiotherapy. When treating lung cancer with radiotherapy, some dose is inevitably given to the heart. Cardiac toxicity after radiotherapy is well-described in patients with breast cancer and Hodgkin's lymphoma. There is emerging evidence that cardiac toxicity in LA-NSCLC patients is an evolving concern.

## 8. Objectives

This study will test the association between the survival of locally advanced non-small cell lung cancer patients versus irradiation of lung, heart, and cardiac substructures. All patients are treated with definitive radiotherapy between 2014-2015.

Parameters included for the analysis were age, sex, ECOG Performance Status (PS), Body Mass Index (BMI), stage dichotomized in IIb category and  $\geq$ IIIA or recurrence, packyears, logarithmic Gross Tumor Volume (log GTV), dose to GTV based on Equivalent Dose in 2 Gy fractions (EQD2), coronary artery calcium score divided into the four groups (0,1-100, 100-399, $\geq$ 400) and prior heart disease. Additionally, irradiation doses to the heart, lungs, and heart substructures based on Principal Component Analysis (PCA) are included.

The variables included in the model will be chosen utilizing the best subset selection and out-of-boot bootstrap values for cross-validation. The selected multivariable model will be the model that performs the best during cross-validation. None of the variables are forced into the model.

# Section 3: Trial methods

## 9. Trial design- description of trial design

The study is a national retrospective observational study of NSCLC patients treated with curative RT in all oncology departments in Denmark.

## 10. Randomization

Not relevant, a retrospective study.

## 11. Sample size

This study is on the same cohort as the previous one, so we have not performed a detailed sample size calculation.

## 12. Framework

The primary objective is to identify patients at risk suspecting that patients with the highest irradiation dose to the heart and its substructures have worse overall survival. If the patients have a worse overall survival based on irradiation dose will have a Hazard Ratio (HR) deviating significantly from one.

## 13. Statistical Interim analysis and stopping guidance

Not relevant, as this is a retrospective analysis.

## 14. and 15. Timing of final analysis and outcome assessments

The patients were treated in 2014-2015; the analysis is planned for 2023, and the CACS analysis was performed during 2020 and 2021. The death date was retrieved from the Danish Lung Cancer Registry in the fall of 2022. We have at least five years of follow-up in data analysis and retrieval. Data on irradiation dose to the heart is retrieved on May 2023.

# Section 4: Statistical Principles

## 16.-18. Confidence Intervals and p-values

All confidence intervals will be based on the 95% confidence interval. The cross-validation method for parameter selection is not based on specific p-values.

## 19. Adherence and protocol deviations

In a retrospective study, no protocol deviations are expected.

## 20. Analysis population

Patients with NSCLC received the first RT fraction from January 1, 2014, until December 31, 2015. The patients are treated at all RT centers in Denmark (Odense, Aalborg, Aarhus, Vejle, Herlev, and Rigshospitalet). Patients are diagnosed with locally advanced NSCLC and treated with a prescribed dose of at least 24 fractions and 50 Gy, with or without chemotherapy. The patient cohort is the same as in the accepted manuscript [2].

# Section 5: Trial population

## 21. – 23. Screening data, eligibility, and recruitment

Patients are identified at the different centers (as seen in part 20) using radiotherapy diagnosis codes. All patients treated with definitive radiotherapy with or without chemotherapy, between 50 -66 Gy dose to Clinical tumor volume delivered, in 24-33 fractions will be included in the study. A non-contrast CT is required for performing a CAC analysis. Patients that do not have a non-contrast CT will generate missing data on CAC scores and will be excluded from the study. (see part 28). The CT scan used for CAC scoring s performed 0-3 months before radiotherapy treatment.

CAC scoring was performed in late 2020 and terminated in January 2022 on planning CT scans. CAC scoring is performed manually using the Agatston method (This part is described in detail In SAP 1 and Article 1).

Patients in a prospective study (NARLAL II – NCT02354274) are omitted.

Calcium scoring is performed at the four coronary arteries (Left main coronary artery, left descending coronary artery, circumflex artery, and right coronary artery).

Heart and substructures are automatically delineated based on Danish National Guidelines on heart and substructure delineation. The delineation of the heart and substructures is based on a hybrid method, utilizing the nn-Unet algorithm for whole heart delineation and atlas-based segmentation for the delineation of substructures (based on a manuscript under preparation by Olloni et al.).

## 24. Withdrawal/Follow-up – level of withdrawal

In a retrospective study, no withdrawal is expected.

## 25. Baseline patient characteristics

Baseline patient characteristics included in the study are, among others, age, sex, performance status, weight, BMI, Gross tumor volume, stage dichotomized in IIb category and  $\geq$ IIIA or recurrence and packyears, dose in 2 Gy equivalent dose using alpha/beta ratio of 10 Gy (EQD2) subdivided by CACs group.

Data on cardiac disease before radiotherapy treatment are gathered from the Danish National Patient Register (LPR). Data on causes of death are gathered from the Cause of Death Register.

Data from LPR and the Cause of Death Register will be delivered from Statistics Denmark in the summer of 2022. Data from LPR consist of data from the patients ten years prior to radiotherapy treatment and up to 3 years after completion of radiotherapy treatment (Until December 31, 2018).

Heart diagnosis is defined based on the ICD 10 codes in Table 1:

| Diagnosis                                                  | ICD-10 code                                   |
|------------------------------------------------------------|-----------------------------------------------|
| Hypertensive diseases                                      | I10-I16                                       |
| Conduction disorders Cardiac arrhythmia and cardiac arrest | I44-I46 I47-I49                               |
| Atrial fibrillation (and atrial flutter)                   | I48                                           |
| Pulmonary embolism                                         | I26-I28                                       |
| Heart failure                                              | I50                                           |
| Peri myocarditis +/- effusion                              | I30-I32 I40-I43                               |
| Valvular disease                                           | I34-I37, I39                                  |
| Myocardial infarction                                      | I21 I23, including KFNA-E and KFNG procedures |

|                     |         |
|---------------------|---------|
| Cerebral Infarction | I63-I64 |
| Diabetes            | E10-E14 |

Table 1 ICD-10 codes used for the definition of cardiovascular heart disease

Prior heart disease is classified into two variables.

- Variable 1 -Baseline risk factors dichotomized in none or Hypertensive disease/Diabetes.
- Variable 2- Baseline heart disease is divided into subgroups:
  - Group 1; No baseline cardiac disease.
  - Group 2; Heart Failure, Myocardial Infarction, Valvular Disease, Cerebral Infarction, Peri myocarditis, and Effusion.
  - Group 3; Conduction disorders, Atrial fibrillation (and flutter).

## Section 6: Analysis

### 26. Outcome definitions

Survival status (Alive/dead) and potential death date are retrieved from the Danish Lung Cancer Registry and delivered from the Danish Civil Registration System. Survival time is calculated from the date of the simulation scan until the date of death. Patients are right-censored if still alive at the retrieval of death dates from the Registry.

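### Survival is timed from the simulation scan although cohort entry comes later, and Sections 20 and 21–23 disagree on whether entry rests on prescribed or delivered dose

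*SAP*

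**What the plan says.** **Time origin.** Section 26: "Survival time is calculated from the date of the simulation scan until the date of death". The only other rule on follow-up is "Patients are right-censored if still alive at the retrieval of death dates from the Registry". Section 27 fits Cox models. The SAP nowhere mentions delayed entry, left truncation or a landmark.

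**Entry, Section 20.** "Patients with NSCLC received the first RT fraction from January 1, 2014, until December 31, 2015". The dose criterion is "treated with a prescribed dose of at least 24 fractions and 50 Gy, with or without chemotherapy", with no upper limit. The section adds that the cohort is that of the accepted manuscript.

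**Entry, Sections 21–23.** Patients with "between 50 -66 Gy dose to Clinical tumor volume delivered, in 24-33 fractions will be included in the study". This rule speaks of delivery and has an upper limit.

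**Gap from scan to treatment.** Sections 21–23: "The CT scan used for CAC scoring s performed 0-3 months before radiotherapy treatment". The same sections say that calcium was scored on planning CTs. I take the planning CT to be the simulation scan; the SAP does not say so outright.

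**The concern.** There are two linked problems.

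1. The clock starts before a patient can qualify. Someone who dies between scan and first fraction is never in the cohort, yet each included patient contributes time at risk over that interval. Its length differs between patients, so the early risk sets contain people who had not yet entered.

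2. The two eligibility rules define different cohorts. A patient prescribed a qualifying course who dies or stops before 24 fractions is in under Section 20 and out under a literal reading of Sections 21–23. Section 12 asks whether higher dose to the heart and its substructures goes with worse survival. Excluding patients for what happened after exposure began is selection on a consequence of treatment, and moving the time origin does not bring them back.

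**Working it through.** The SAP gives no event count, median survival, gap distribution or sample size calculation, so there is no figure of its own to reproduce.

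**Inputs from the SAP:** gap 0–3 months (up to about 13 weeks); 24–33 fractions; N = 644 (example table of patient characteristics).

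**Assumptions:** five fractions a week; exponential survival; median survival of 18, 24 or 36 months; for the on-treatment count, death rates of 0.19–0.30 per year.

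**Step 1: length of the interval before entry.**
- Entry at first fraction: 0 to about 13 weeks.
- Entry on delivered dose: add 24/5 = 4.8 to 33/5 = 6.6 weeks, giving about 5 to 20 weeks in all.

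**Step 2: share of scanned patients who die before entry,** 1 − 0.5^(w/median), with w converted at 4.345 weeks per month.

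| Interval w | Median 18 mo | 24 mo | 36 mo |
|---|---|---|---|
| 4 weeks (gap only) | 3.5% | 2.6% | 1.8% |
| 13 weeks (longest gap) | 10.9% | 8.3% | 5.6% |
| 4 + 6.6 weeks (delivered) | 9.0% | 6.8% | 4.6% |
| 13 + 6.6 weeks (delivered, extreme) | 16.0% | 12.2% | 8.3% |

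**Step 3: effect on the dose hazard ratio.** The simulation used 300 runs per setting, n = 644, a true hazard ratio of 1.20 per SD of dose, a gap uniform on 0–4 or 0–13 weeks, and a gap–dose correlation of 0 or ±0.3. It was run with and without the treatment weeks. Each data set was fitted three ways.

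| Cox fit | Hazard ratio across settings |
|---|---|
| From scan, no delayed entry (as planned) | 1.184–1.212 |
| From scan with delayed entry, or from entry | 1.196–1.207 |

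Within a setting, the largest difference between the planned fit and the delayed-entry fit is about 0.013 (for example 1.184 against 1.197, and 1.212 against 1.199). It goes either way, depending on the sign of the correlation. With zero correlation the fits agree to three decimals. With gaps of at most 4 weeks the difference does not exceed 0.004. The effect is small because only events in the first weeks on the time scale have wrong risk sets; after that everyone has entered.

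**Step 4: effect on absolute survival.** In the same runs, median survival from the scan rose by about 0.3 months (gap up to 4 weeks, entry at first fraction) to about 3 months (gap up to 13 weeks plus full delivery).

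**Step 5: deaths in the treatment weeks alone,** if delivery is required.
- Low: 1 − exp(−0.19 × 4.8/52) = 1.7%; 644 × 0.0174 ≈ 11.
- High: 1 − exp(−0.30 × 6.6/52) = 3.7%; 644 × 0.0374 ≈ 24.

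This is not a bound. An 18-month median, as in Step 2, gives 644 × (1 − 0.5^(6.6/4.345/18)) ≈ 37 for 6.6 weeks. Patients who stopped early but survived would come on top and cannot be estimated. Nor does the simulation cover dose-related deaths during treatment.

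**The case against.** The best defence is that the planned target is a hazard ratio (Sections 12 and 27), which hardly moves. The text shown plans no median or absolute survival estimate, and nothing in the SAP links the gap to dose. That stands, and it limits the time-origin part to an inexpensive correction. The scan is also a defensible origin, being the CT on which calcium is scored, provided delayed entry goes with it.

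A reader might infer classic immortal time bias, in which one dose group is credited with guaranteed survival. The documents do not support this: the entry condition is the same for every patient. A reader might also infer that the dose hazard ratio is pulled toward one. The simulated shifts fall on both sides of 1.20, and the SAP has no data on dose-related deaths during treatment.

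On eligibility, the defence is that the delivered-dose sentence is loosely worded and may only describe the regimen, and that Section 20, which is the analysis-population section, says prescribed. That is a fair reading, so one cannot assert that on-treatment deaths were removed. But the text does not settle it, and the reference to the earlier manuscript does not say which rule was applied there.

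**Conclusion.** The point holds in limited form. Time zero precedes cohort entry and the Cox model makes no allowance for it. Absolute survival from the scan is inflated by about 0.3 to 3 months under the assumptions above; the dose hazard ratio shifts by at most about 0.013 on 1.20, and only if gap and dose are related. Those sizes rest on assumed exponential survival, proportional hazards, gap distributions and medians.

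The contradiction between Sections 20 and 21–23 is the more consequential part, because it decides whether deaths and stops during radiotherapy are analysed. If the delivered-dose rule is literal, roughly 11–24 deaths on a base of 644 would be at issue at rates of 0.19–0.30 per year, more if early mortality is higher. The size and direction of any resulting bias in the hazard ratio cannot be derived from the SAP.

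**What to change.** - **Section 26:** start survival at the date of the first fraction, which is already needed for inclusion. Alternatively, keep the scan as origin and enter patients into the risk set at the first fraction.
- **Sections 20 and 21–23:** reconcile prescribed against delivered, and the presence of an upper limit, so that one rule defines the cohort. State whether deaths and stops during radiotherapy are included.
- **If completed delivery really is required:** start follow-up at the end of radiotherapy (landmark), report how many patients the rule excluded, and limit the conclusion to patients who completed treatment. Delayed entry at the last fraction would correct the risk sets but would not restore the excluded deaths.

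The cost is a few lines of SAP text and one date variable. Survival times become slightly shorter, and the origin may differ from that of the earlier analysis of this cohort, which the SAP does not state. Timing from the scan can be kept as a sensitivity analysis. Section 2 says that heart dose had not been analysed when the SAP was completed, so a dated amendment before that analysis would not be driven by the dose results.

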### 27. Analysis methods

Appendix 2 is an overview of the table of patient characteristics in the publication and the expected figures. Furthermore, some figures that explain the PCA components chosen will be visualized.

Age, BMI, GTV, pack years, and Dose EQD2 will be summarized by median and IQR. The remaining variables are categorical and will be summarized by numbers and percentages.

Based on Bootstrap, the adjusted multivariable model will be selected, where the cross-validation will be performed at the out-of-boot patients. Before each Bootstrap, the missing data are imputed (see below), thereby using multiple imputations. For each Bootstrap, Cox proportional hazard models are made for all possible subsets of models (all combinations of variables during the model selection). For each model, a cross-validated likelihood is calculated utilizing the patient data not included in the Bootstrap (out-of-boot patients). Since there will be a varying number of out-of-boot patients, the cross-validated values will be scaled based on the number of out-of-boot patients, as suggested by Schemper et al.[3]. For the parameter selection, 50 bootstraps will be performed, and the cross-validated value will for each model be averaged over the 50 boots.

For the multivariable model, confidence intervals of the regression constants are obtained using the profile likelihood based on the 2000 bootstraps of the model. For all the variables, the confidence interval is reported as two-sided; the confidence interval will be defined by the central 95% of the bootstrapped values.

As mentioned in Objective (8): Parameters included for the analysis are age, sex, ECOG Performance Status (PS), Body Mass Index (BMI), stage dichotomized in IIb category and  $\geq$ IIIA or recurrence, packyears, logarithmic Gross Tumor Volume (log GTV), dose to GTV based on Equivalent Dose in 2 Gy fractions (EQD2),

coronary artery calcium score and prior heart disease. Additionally, irradiation doses to the heart, lungs, and heart substructures based on Principal Component Analysis (PCA) are also included (see further under part 27.1)

A table with unadjusted univariable Hazard ratios by COX regression and the same table containing adjusted Hazard ratios will be reported. The table will be shown as numbers with a 95 % Confidence Interval and as a forest plot.

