For the current trial, the principal components selected will account for at least 95% of the variance in the original data. However, a maximum of eight principal components will be included in the model selection process to ensure efficient parameter selection based on the best-subset method (as described in section 27, Analysis Methods). Consequently, the PCA method reduces the initial 350 correlated numbers per patient to a maximum of 8 uncorrelated values. Once the principal components are determined, the corresponding values for each component per patient are calculated. These values then become part of the model selection process alongside other clinical parameters.

If the computer time at “Forskermaskinen” shows to take above one day, we might be forced to reduce to a maximum of six components.

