## 28. Missing data

Missing data will be reported in Table 1 (Patient Characteristics). Multiple imputations will be performed before each Bootstrap for the best subset analysis. The imputation method is based on Multivariate Imputation by Chained Equations (The MICE package in the R statistical software).

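### Section 27 defines the 95% confidence interval in two incompatible ways and bootstraps an already selected model, so selected dose effects that are weak or null look more certain than they are

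*SAP*

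**What the plan says.** - **Interval.** Section 16-18 sets the level: "All confidence intervals will be based on the 95% confidence interval". Section 27 says the intervals are "obtained using the profile likelihood based on the 2000 bootstraps of the model". Its next sentence says "the confidence interval will be defined by the central 95% of the bootstrapped values".
- **Selection.** Section 8: "The selected multivariable model will be the model that performs the best during cross-validation", and "None of the variables are forced into the model". Section 27: "For the parameter selection, 50 bootstraps will be performed". The model that comes out of this step is the one Section 27 calls the adjusted multivariable model. Section 27.1 adds the dose candidates: "a maximum of eight principal components will be included in the model selection process".
- **Use.** Section 12 ties the primary objective to an HR for dose that differs significantly from one. Section 16-18 sets no p-value rule for selection, so the interval carries the inference.
- **Missing data.** Section 28: "Multiple imputations will be performed before each Bootstrap for the best subset analysis". Section 27 mentions imputation before each bootstrap only in the paragraph on model selection.

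**The concern.** Two analysts could follow Section 27 faithfully and report different limits, because the text names two procedures for the same interval.

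The interval is also computed as if the model had been fixed in advance. The dose components are the exposure of interest, yet they compete for entry like any other variable. A component with little or no true effect enters mainly when its estimate happens to be large in these patients. Bootstrapping the fixed model afterwards takes no account of that search. The adjusted table would then show a dose HR that is too far from one, with an interval that claims 95% coverage and does not have it. That is the quantity from which Section 12 draws its conclusion.

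**Working it through.** **1. The two definitions.** A profile-likelihood interval inverts a likelihood-ratio test on one fitted data set and needs no resampling. A percentile interval takes the 2.5th and 97.5th percentiles of the resampled estimates (values 50 and 1950 of 2000). Neither yields the other. The conflict leaves the method undefined but does not push the limits in a known direction.

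**2. Size of the search.** Section 8 lists ten clinical parameters, and Section 25 splits prior heart disease into two, giving 11. With up to 8 components there are 19 candidates and 2^19 = 524,288 subsets. Nothing in Section 27 says the search is repeated in the 2000 resamples.

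**3. Null component, by formula.** Suppose a term enters when |z| > c, with c below 1.96. For a true log HR of 0, a nominal 95% interval misses in 5% of all runs, and all of those misses are runs in which the term entered. So coverage given selection = 1 − 0.05 / P(selected).
- c² = 2 (AIC-like): P(selected) = 0.157; 1 − 0.05/0.157 = 68%.
- c² = 3: P(selected) = 0.083; 1 − 0.05/0.083 = 40%.

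This result does not depend on the number of deaths.

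**4. Simulation of the planned procedure.** Inputs: n = 644 (example table), 75% deaths = 483 (assumed), five independent standardised covariates, all 32 subsets scored by out-of-boot partial likelihood over 50 bootstraps, then percentile intervals from 400 bootstraps of the chosen model; 600 replicates.

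| True log HR per SD | Selected | Coverage if selected | Coverage, full model |
|---|---|---|---|
| 0 (two terms) | 9% | 48% | 95% |
| 0.05 | 26% | 89% | 95% |
| 0.10 | 67% | 95% | 94% |
| 0.20 | 99% | 96% | 96% |

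The full model without selection thus reproduces the nominal 95%. The 48% rests on 52 and 54 selected runs for the two null terms, so about ±14 points each. A second Cox simulation (about 494 deaths assumed, 1500 replicates per scenario) gave 52% for a selected null component, again selected in 9% of runs. In it, a true log HR of 0.08 had a mean estimate of 0.115 among selected runs: 0.035/0.08 = 44% too large.

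**5. Range for the unknown death count.** For a standardised term, SE ≈ 1/√deaths. Using the selection rule with c² = 3, whose selection rates are close to those simulated:

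| Deaths (assumed) | SE | Coverage at 0.05 | Coverage at 0.10 |
|---|---|---|---|
| 60% = 386 | 0.0509 | 88% | 96% |
| 75% = 483 | 0.0455 | 90% | 96% |
| 90% = 580 | 0.0415 | 91% | 97% |

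The pattern is stable over this range.

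**6. How often a null component enters.** With 8 independent null components, the chance that at least one is selected is 1 − (1 − 0.083)^8 = 50% at c² = 3, and 1 − (1 − 0.157)^8 = 75% at c² = 2.

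**7. Imputation.** The example table shows stage missing in 35 and performance status in 6 of 644 patients, so 35 to 41 patients are affected, depending on overlap (5.4% to 6.4%). If one imputed data set were reused as though observed, the SE for stage would be understated by at most √(1/(1 − 35/644)) = 1.028, or 2.8%. If patients with either value missing were dropped, intervals would widen by up to √(1/(1 − 41/644)) = 1.033, or 3.3%.

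**The case against.** **The tempting stronger reading is that all the reported intervals will be too narrow.** The SAP does not support that. The clash of definitions has no direction. Clearly prognostic variables keep about 95% coverage. For weak terms, much of the failure is bias in the estimate that survives selection rather than interval width. Dropping incomplete patients would widen intervals, not narrow them.

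**The false-positive rate per component is not inflated in the independent case.** A null component that is selected and also excludes HR = 1 occurs in 0.09 × 0.52 = 4.7% of runs (0.093 × 0.482 = 4.5% in the second simulation), about the nominal 5%. This stands, and the 50% figure must be read with it: it describes the interval once a component has been selected. That is still the interval the reader of the adjusted table sees. Testing several components at once is a separate multiplicity question.

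**Imputation may be intended throughout.** A reader might infer that the interval step uses complete cases or one fixed imputation. The SAP says neither, and the wording in Section 27 could be read to cover the 2000 resamples. Nor does the example table show a loss of 90 patients (6 + 35 + 49): the 49 are missing smoking history, which is not a candidate. Pack-years is a candidate, and its missingness is not given.

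**The second sentence on the interval gives a workable rule.** True, but the sentence before it still names another method.

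**Conclusion.** The point holds in a limited form. Section 27 gives two incompatible interval definitions and, on its plain reading, bootstraps a model selected on the same patients. For dose components with a weak or null effect that survive selection, the HR is exaggerated and the interval overconfident: coverage about 50% for a null term and 89% at a log HR of 0.05 per SD. From 0.10 upward, coverage is about 95%. This matters because Section 12 rests the conclusion on that interval.

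The sizes assume independent covariates, five candidates rather than up to 19, and a death count the SAP does not give. The direction for null terms follows from the formula alone. The gap on imputation is real but minor.

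**What to change.** 1. **Section 27, interval.** Delete the reference to profile likelihood. Define the interval as the 2.5th to 97.5th percentiles of 2000 bootstrap estimates.
2. **Section 28.** State that missing data are imputed for each of those 2000 resamples as well as for the best-subset step.
3. **Sections 12 and 27, dose inference.** Report HRs and intervals for all retained dose components from the full prespecified model (all clinical variables and all components, no selection), and base the significance statement in Section 12 on it.
4. **Best-subset model.** Keep it as the prediction model, with its intervals labelled as conditional on selection.

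The cost is SAP wording, a little more analysis work and wider intervals for the dose terms. Section 2 states that no analysis of heart dose had been done when the SAP was completed.

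Rerunning the subset search in every resample is not required. It would take 2000 × 50 × 524,288 ≈ 5.2 × 10^10 Cox fits per model, against 50 × 524,288 ≈ 26 million planned, and Section 27.1 already foresees cutting components if computing exceeds one day. The coverage of such intervals was not checked here.

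### Dose is the exposure under test, yet it enters only as droppable components, so the association objective may end without an adjusted HR, and weak effects that are kept are overstated on average

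*SAP*

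**What the plan says.** - **Aim.** SAP Section 8: "This study will test the association between the survival of locally advanced non-small cell lung cancer patients versus irradiation of lung, heart" and cardiac substructures. Section 12 makes dose to the heart and its substructures the primary exposure and sets the criterion: patients with worse survival because of dose "will have a Hazard Ratio (HR) deviating significantly from one".
- **How dose enters.** Section 27.1 runs a principal component analysis (PCA) jointly on the DVHs of lungs, whole heart and heart chambers (primary model), or of lungs, whole heart and coronary arteries (second model). At most eight components are kept, possibly six. Of the patients' component values it says: "These values then become part of the model selection process alongside other clinical parameters".
- **Selection.** Section 27: "Cox proportional hazard models are made for all possible subsets of models (all combinations of variables during the model selection"). Section 8 adds "The selected multivariable model will be the model that performs the best during cross-validation" and "None of the variables are forced into the model".
- **Output.** Section 27: "A table with unadjusted univariable Hazard ratios by COX regression and the same table containing adjusted Hazard ratios will be reported", with 95% confidence intervals and a forest plot. Intervals for the multivariable model come from 2000 bootstraps of that model.
- **Nothing else.** Section 29 plans no further analysis of this cohort.

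**The concern.** An association objective needs an adjusted estimate of the exposure whatever its size. Here the exposure is treated as one more candidate predictor. All combinations are searched, including those with no dose component, and the selected model is the only adjusted model defined.

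Two things follow. First, a component that is not selected has no adjusted HR or interval, and Section 27 has no rule for its row in the adjusted table. The result would then be reported as not selected, with nothing adjusted for tumour volume, stage or performance status to show how much harm was excluded. Second, a component that is selected is seen only because its estimate was large enough to survive. Section 27 does not say that the 2000 bootstraps repeat the search, so the intervals need not reflect it.

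**Working it through.** The SAP gives no sample size calculation (Section 11), event count or effect size, so there is no figure of its own to reproduce. The selection rule was simulated instead.

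**Inputs.** N = 644 (example table of patient characteristics); 50 selection bootstraps and out-of-boot likelihood scaled by the number of out-of-boot patients (Section 27); at most eight components (Section 27.1). Assumed: 60% or 80% deaths (0.6 × 644 = 386; 0.8 × 644 = 515) and a true HR per SD from 1.00 to 1.30.

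**Method.** One standardised component, 1000 runs per setting. It is kept if its mean out-of-boot partial log-likelihood beats the model without it. The HR is then estimated on all patients, with a Wald 95% interval standing in for the bootstrap interval.

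| True HR per SD | Dropped, 60% / 80% deaths | Mean HR if kept | log HR if kept ÷ true log HR |
|---|---|---|---|
| 1.00 | 92% / 91% | 1.11 / 1.09 (size in either direction) | n/a |
| 1.05 | 78% / 74% | 1.11 / 1.10 | 2.2 / 2.0 |
| 1.10 | 45% / 34% | 1.14 / 1.13 | 1.38 / 1.25 |
| 1.15 | 17% / 7% | 1.16 / 1.16 | 1.08 / 1.03 |
| 1.20 | 3% / 1% | 1.20 / 1.20 | 1.02 / 1.00 |
| 1.30 | 0% / 0% | 1.30 / 1.30 | 1.01 / 1.01 |

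A separately coded simulation at 80% deaths (500 runs per case) dropped HR 1.05, 1.10 and 1.15 in 74%, 31% and 8% of runs. For HR 1.10 the range is therefore 31-45%. That effect is not trivial: between the means of the top and bottom quarters it is exp(2.54 × ln 1.10) = 1.27.

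**Chance that all eight are dropped**, treating the components as independent:
- No effect in any: 0.923^8 = 53% (60% deaths); 0.914^8 = 49% (80% deaths).
- HR 1.05 in each: 0.779^8 = 14%; 0.743^8 = 9%.
- One at 1.10 and seven null, 80% deaths: 0.31 × 0.914^7 = 17% (18% with the table's unrounded 0.337). At 60% deaths: 0.446 × 0.923^7 = 25%.

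**What non-selection shows.** At 80% deaths, the null retention rate of 8.6% corresponds to a threshold of |z| about 1.73, with SE = 1/√515 = 0.044. At true HR 1.10 the expected z is 0.0953/0.044 = 2.16. The 95% interval reaches 1.10 when z is at least 2.16 − 1.96 = 0.20. Among dropped cases that share is [Φ(−0.43) − Φ(−1.96)]/Φ(−0.43) = (0.333 − 0.025)/0.333 = 92%. The simulated share was 95%. Being dropped therefore does not exclude an effect of that size.

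**Intervals after selection.** Among kept components, coverage of the 95% interval is 55% / 51% at true HR 1.00, about 91% at 1.05, and 95% or more from 1.10. At true HR 1.00, 46% / 49% of kept components have an interval that excludes one.

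**With the component always in the model** (same data), mean HRs are 1.05 and 1.10 at those true values, and coverage is 95-97% in all settings.

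**The case against.** The strongest defence is that the search is deliberate and suits a predictive aim. Section 2 speaks of predicting overall survival, Section 12 of identifying patients at risk, and Section 27.1 of a predictive model. Under that aim, dropping dose is a legitimate result. This stands as a reason to keep the search. It does not answer Sections 8 and 12, which commit to testing an association by an HR.

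Four stronger readings that a reader might infer are not supported:
- *Every kept HR is inflated.* The bias is an average, conditional on selection. It matters for null or weak effects, and the SAP does not say whether the true effects are weak.
- *A dropped component has no interval at all.* Section 27 still reports its unadjusted HR with a 95% interval. Only the adjusted estimate is missing.
- *The single-component drop rates are the risk to the primary objective.* They are not. Losing every component is likely only when none has an effect. If each of eight had HR 1.10, the chance is under 0.1% at 80% deaths (0.31^8).
- *The components are heart dose.* Each PCA includes the lungs, so no component is defined as heart dose alone. An adjusted HR per component is not a heart-only effect either.

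The simulation is also simpler than the plan: one component at a time, no clinical covariates, no imputation. PCA makes the components uncorrelated with each other, but not with tumour volume or other covariates.

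**Conclusion.** The structural point follows from the text alone: carried out exactly as written, the plan can leave its primary exposure with no adjusted HR or interval. How often depends on figures that the SAP does not give. Under 60-80% deaths and independent components, it is about half of studies with no dose effect, about 9-14% with HR 1.05 in every component, and about 17% (80% deaths) to 25% (60% deaths) with one component at 1.10 and seven null. The bias in kept components roughly doubles the log HR at 1.05, multiplies it by 1.25 to 1.4 at 1.10, and is negligible from 1.20.

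This is a mismatch between aim and method that should be fixed. It does not invalidate the search as a predictive exercise.

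**What to change.** In Sections 12 and 27:
- Base the association objective on one pre-specified Cox model per DVH set, containing all listed clinical covariates and all retained dose components.
- Report the adjusted HR per SD with its 95% interval for every component, selected or not.
- Present each HR with the component's loadings, and do not read it as a heart-only effect.
- Keep best-subset selection as a secondary predictive analysis, and state that non-selection is not evidence of no association.

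The cost is some SAP wording, one extra model per DVH set and somewhat wider intervals than a reduced model gives. The model has about 22 parameters: 8 single terms + 3 for calcium score + 1 for risk factors + 2 for prior heart disease + 8 components. That leaves 386/22 = 17.5 to 515/22 = 23.4 deaths per parameter at 60-80% deaths.

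Forcing only the dose components into the search would also guarantee an adjusted HR, but the adjustment set would still be chosen by the data.
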